### Assessment endpoints

Density incidence of major catheter-related infection, catheter colonization, catheter-related bloodstream infection, and skin colonization at catheter insertion site for all catheters and for arterial or central venous catheters only; mortality rate in ICU and in the hospital; length of stay in ICU and in hospital; incidence of cutaneous allergy using the International Contact Dermatitis Research Group scale [17]; cost of each strategy of skin preparation.

### Sample size calculation

Assuming 5% of catheter-related infection rate in the 5% povidone iodine/69% ethanol group (that is, incidence density of 4 per 1,000 catheters days) and the use of at least two catheters per patient on average, 453 patients in each treatment arm will be required to demonstrate a 50% reduction of major catheter-related infection with the use of 2% chlorhexidine/70% isopropyl alcohol, with a power of 80% and a two-sided alpha risk of 5%. We plan to enroll 2,400 patients (4,800 catheters) to take into account the interaction between antiseptic efficacy and skin scrubbing and a maximum patient loss of 6%.

### Statistical analysis

The data will be analyzed blindly with regard to treatment arms. An intention-to-treat analysis is scheduled, and it will include all patients except those with no catheter inserted and those who will have withdrawn their consent to participate in the study. No interim analyses are planned. Demographic data will be described in number and percentage or median and interquartile range for quantitative and qualitative variables and compared with χ^2^ test or Mann–Whitney, as appropriate. Kaplan-Meir curves of the risks of major-CRI and CR-BSI and catheter colonization will be plotted for each treatment group. Proportional hazard assumption will be assessed by plotting Schoenfield’s residuals with time.

Analysis of antiseptic efficacy will be carried out using a marginal Cox model stratified by centers [18]. This model takes into account the censored nature of the data and also accounts for intra-cluster (intra-patient) dependence (more than one catheter per patient) using a robust sandwich covariance matrix. The interaction between scrubbing and antiseptic effect will be sought first by forcing the interaction term in the final model. In the absence of interaction, analysis of skin scrubbing and chlorhexidine effects will be performed independently. For secondary endpoints the analyses will not be controlled for multiple testing.

Comparisons of skin cultures between groups will be assessed through multiple factor ANOVA (Center, scrubbing, antiseptic).

Analyses will be done using SAS 9.x (SAS Institute, Cary, NC,USA) and R (R foundation, Vienna, Austria) softwares.

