## Methods

### Ethics statement

The study was approved by the local ethics committee (CPP Ouest III, France) on 21 May 2012 (Protocol# 12.02.06). Each patient will have oral and written information concerning the study design and outcomes. If the information cannot be delivered to the patient, it will be delivered to his/her relatives.

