### Study design

The CLEAN study is a prospective multicenter, 2×2 factorial, randomized-controlled, assessor-blind trial involving 11 intensive care units in five French University-affiliated hospitals and one French general hospital and is designed to compare two antiseptics (2% chlorhexidine/70% isopropyl alcohol and 5% povidone iodine/69% ethanol) with or without prior skin scrubbing. Due to the different colors of the two solutions, nurses and physicians will not be blinded to the antiseptic agent used. However, the microbiologists assigned to process all of the cultures and the adjudication committee tasked with reviewing the outcomes other than colonization will be unaware of the patients’ arms.

Inclusions opened at the end of October 2012 and will close approximately 14 months later.

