### End of participation in the study

A patient will leave the study if he (she) refuses to participate to it, if an exclusion criterion appears during hospital stay, if a severe adverse event occurs or if there is an allergy to one of the antiseptic agents.

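### The analysis called intention-to-treat drops every patient who withdraws consent, losing outcomes seen before withdrawal that the planned Cox model could keep by censoring

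*Protocol article*

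**What the plan says.** The Statistical analysis section announces an intention-to-treat analysis and defines its population: "it will include all patients except those with no catheter inserted and those who will have withdrawn their consent to participate in the study". The article does not provide for keeping data gathered before withdrawal. It also does not limit the exclusion to patients who refuse use of their data; the stated trigger is withdrawal of consent to take part.

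Four other statements bear on the point:

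- The same section chooses a marginal Cox model and says of it: "This model takes into account the censored nature of the data".
- End of participation in the study opens its list of reasons for leaving with refusal: "A patient will leave the study if he (she) refuses to participate to it". It then lists a newly arising exclusion criterion, a severe adverse event and allergy to an antiseptic. None of these other reasons is an exclusion from the analysis set.
- Study design calls the trial assessor-blind and states that "nurses and physicians will not be blinded to the antiseptic agent used". Microbiologists and the adjudication committee do not know the arm.
- The Ethics statement says: "If the information cannot be delivered to the patient, it will be delivered to his/her relatives".

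**The concern.** The two exclusions differ in kind. A patient in whom no catheter was placed has no catheter outcome to lose. A patient who withdraws may already have contributed catheters with complete, adjudicated results, and the rule deletes them.

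This is a selection made after randomization, by a process that can know the arm. Staff see which antiseptic is used, and the scrubbed and unscrubbed procedures differ visibly. It is a reasonable inference, though not stated, that some refusals come once catheters are in place and something has happened, such as mild skin irritation or a suspected infection. The category recorded for a departure also matters: a patient with a skin reaction stays in the analysis if the reason entered is allergy, and disappears if it is withdrawn consent.

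If withdrawal depended on both arm and outcome, the comparisons of infection, colonization and cutaneous tolerance would be biased. Even if it did not, the analysis set would not be the intention-to-treat set that its label promises.

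**Working it through.** **Inputs from Sample size calculation.** Infection rate of 5% per catheter on povidone iodine, equated to 4 per 1,000 catheter-days; 50% reduction, so 2.5% on chlorhexidine; two catheters per patient; 80% power, two-sided 5%; 2,400 patients, 4,800 catheters. Allocation is 1:1:1:1 (Randomization), so each antiseptic has 1,200 patients and 2,400 catheters.

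**Assumption.** The withdrawal rate is not given. I use 1% to 3%.

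**The plan's own figure.** The usual two-proportion formula (pooled variance under the null, no continuity correction) gives, with mean rate 0.0375:

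n = [1.96 × √(2 × 0.0375 × 0.9625) + 0.842 × √(0.05 × 0.95 + 0.025 × 0.975)]² / 0.025² = 906 catheters per arm.

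906 / 2 = 453 patients, as stated. The inputs are therefore read correctly. Like the plan, this treats catheters as independent.

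**Expected infections.** 2,400 × 0.05 + 2,400 × 0.025 = 120 + 60 = 180, an average of 3.75% per catheter. The two forms of the control rate imply 0.05 / 0.004 = 12.5 days per catheter.

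**What the exclusion removes, at average risk.**

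| Withdrawal (assumed) | Patients | Catheters | Catheter-days (× 12.5) | Infections (× 3.75%) |
|---|---|---|---|---|
| 1% | 24 | 48 | 600 | 1.8 |
| 3% | 72 | 144 | 1,800 | 5.4 |

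These are upper bounds on what the fix would recover at average risk, because each withdrawer is credited with two full catheter courses and only the time before withdrawal could be kept. The infection count would be higher if withdrawal tended to follow an infection.

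**Power for the antiseptic main effect.** Solving the same formula for power gives 99.5% with all 2,400 patients and 99.4% with 2,328 (3% removed). Precision is not at stake.

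**Bias, by illustration.** Suppose there is no true effect, the rate is 5% in both antiseptic arms, and a share w of one arm only withdraws, with m times the average infection risk. Excluding them moves the rate ratio from 1.00 to (1 − w × m) / (1 − w):

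- w = 1%, m = 2: 0.98 / 0.99 = 0.99
- w = 3%, m = 2: 0.94 / 0.97 = 0.97
- w = 3%, m = 3: 0.91 / 0.97 = 0.94
- any w, m = 1: 1.00

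Bias therefore needs withdrawal to be related to risk and unequal between arms.

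**The case against.** The strongest reply has five parts.

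*The trial is not open-label.* A reader might infer that it is, and that patients and outcome assessors know the arm. The documents do not support this. The design is a "randomized-controlled, assessor-blind trial involving 11 intensive care units", cultures and adjudication are blinded, and only nurses and physicians are said to be unblinded. Patient awareness is plausible, since kits and a poster are in the room, but it is an inference. What remains is that blinded classification protects how an episode is labelled, not who stays in the analysis set.

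*The clearest arm-related departures are not excluded.* Allergy and severe adverse events are separate reasons for leaving, and the analysis set does not drop those patients. This narrows the route to milder intolerance, infection or dislike of the procedure, recorded as withdrawn consent. Nothing in the documents shows that these differ by arm.

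*The 6% loss allowance is not a withdrawal rate.* A reader might apply it and arrive at 144 patients, 288 catheters and 288 × 0.0375 = 10.8 infections. The article calls it maximum patient loss without giving causes, and it may include patients who never had a catheter. It cannot be used to size this point.

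*Exclusion may be required by the consent terms.* Those terms are not shown, and where a patient also refuses use of data already collected, exclusion may be unavoidable. That stands, and the fix allows for it. The rule as written, however, removes everyone who withdraws from participation.

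*Censoring is not a full cure.* If withdrawal is informative, so is censoring at withdrawal. That also stands. Censoring still keeps outcomes already observed, which exclusion throws away.

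**Conclusion.** The point holds as a limited one. The article states a rule that removes whole patients after randomization from a set it calls intention-to-treat, and a less bias-prone alternative fits the model already chosen. This is a stated choice, not a detail left to a fuller document.

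The likely effect is small. At an assumed 1% to 3% withdrawal it concerns at most 24 to 72 patients and, at average risk, about 2 to 5 of some 180 expected infections. Power is essentially unchanged. In the illustration, a null rate ratio moves to between 0.99 and 0.94 when all withdrawals fall in one antiseptic arm at two to three times the average risk; the trial targets a halving. A reader might conclude that the primary comparison is shown to be biased. The documents do not support that: they give no withdrawal rate and no evidence that withdrawal depends on arm or risk. The case rests on an avoidable risk and an inaccurate label.

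**What to change.** Reword the definition of the analysis set in Statistical analysis along these lines:

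- Include every randomized patient with at least one study catheter inserted, in the arm assigned.
- For patients who withdraw consent, keep all data collected before withdrawal and censor catheters still in place on that date in the planned Cox model.
- Exclude data already collected only where the patient or relatives refuse their use.
- Report those exclusions by arm.

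The cost is this wording and one added field recording whether a withdrawal covers further participation only or also data already collected. The Trial status section reports 691 patients already included, so the field may have to be completed retrospectively for any withdrawals among them. The sample size and the model do not change.

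One limit should be acknowledged in the text. Tips are cultured only after removal, so a catheter still in place at withdrawal will usually contribute time but no culture result. The main gain is in catheters removed before withdrawal.

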**Methods:**

A prospective multicenter, 2×2 factorial, randomized-controlled, assessor-blind trial will be conducted in 11 intensive care units in six French hospitals. All adult patients aged over 18 years requiring the insertion of at least one peripheral arterial catheter and/or a non-tunneled central venous catheter and/or a hemodialysis catheter and/or an arterial pulmonary catheter will be randomly assigned to have all their catheters cared with one of four skin preparation strategies (2% chlorhexidine/70% isopropyl alcohol or 5% povidone iodine/69% ethanol with or without prior skin scrubbing). At catheter removal, catheter tips will be quantitatively cultured. Sets of aerobic and anaerobic blood cultures will be routinely obtained when a patient has fever, hypothermia, or other indications. In case of suspected catheter-related infection the patient’s form will be reviewed by an independent adjudication committee. We plan to enroll 2,400 patients (4,800 catheters). The main objective is to demonstrate that use of 2% alcoholic chlorhexidine compared to 5% alcoholic povidone iodine in skin preparation lowers the rate of catheter-related infection. The second endpoint is to demonstrate that enhanced skin cleaning prior to disinfection of skin that is not visibly soiled does not reduce catheter colonization. Other outcomes include comparison of skin colonization at catheter insertion site, comparison of catheter colonization and catheter-related bacteremia taking place during implementation of the four strategies of skin preparation, and cutaneous tolerance, length of hospitalization, mortality, and costs.

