### Catheter insertion and maintenance

All study centers are to follow French recommendations (similar to those of the CDC) for catheter insertion and care. Use of the subclavian vein (except for hemodialysis catheter) and radial artery will be encouraged whenever possible. Catheters will be placed percutaneously using the Seldinger technique. Ultrasound guidance shall be used at the discretion of the attending physician. Before catheter insertion, the skin will be disinfected with the randomized antiseptic procedure assignment. After insertion, catheters will be dressed with semi-permeable non-chlorhexidine transparent dressing. For each unit, the same catheter and dressing types will be used for the duration of the study period. Catheter insertion sites will be inspected every day for signs of infection. Dressing will be changed every 72 h to 7 days according to center protocol or earlier if leaking, soiled, or wet (except for the first dressing changed 24 h after catheter insertion). Manipulation of lines and three-way stopcocks will be carried out with gauze moistened with 5% povidone iodine/69% ethanol in povidone iodine arms and 0.5% chlorhexidine/67% alcohol (Hibitane Champ™, Molnlycke Health Care, Wasquehal, France) in the chlorhexidine arm.

Use of antiseptic-containing dressings, topical antimicrobial ointments, antimicrobial filters, and line locks will not be allowed. Blood sampling through the central venous line will not be permitted. The decision to remove the catheter will be made solely by the patient’s physician, but ablation of the catheter when it is losing its usefulness will be encouraged. Patients leaving the ICU with their central venous catheter will undergo one peripheral and one central line blood culture and will be followed for 3 days after ICU discharge to monitor possible infectious complications. Any catheter infection occurring >3 days after ICU discharge will not be taken into account due to the risk of protocol violation during catheter manipulation or of maintenance by untrained healthcare providers.

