### Cultures

Catheters will be removed aseptically and their distal 5cm will be sectioned with sterile scissors and placed in a sterile tube before being carried to the microbiology laboratory. Catheters will be cultured quantitatively by using a simplified technique of quantitative broth dilution culture [1,14].

Sets of aerobic and anaerobic blood cultures will be routinely obtained when a patient has fever, hypothermia, or other indications such as chills or sudden shock.

Skin colonization will be evaluated before catheter removal by using semi-quantitative insertion-site cultures. The insertion site will be sampled by pressing on the skin for 10 s a sterilized nutritive trypticase-soy agar plate containing antiseptic neutralizing agents (Count-tact™, 3P Pack+, Biomerieux™, Crapone, France).The plate will then be sent to the local microbiology laboratory and cultured for 48 h. The number of colony-forming units will be counted and classified as: sterile; 1 to 9 CFU; 10 to 49 CFU, 50 to 99 CFU, or ≥100 CFU per agar plate as previously done [9,15].

All cultures will be processed by the clinical microbiology laboratory according to standard methods without awareness of the randomization arm.

In cases of suspected catheter-related infection (that is, all the catheters removed with systemic inflammatory response syndrome (SIRS) or local signs of infection (pain or purulence) or positive catheter tip culture, or positive blood culture sampled 48 h before until 48 h after the catheter removal), the patient’s form will be reviewed by an independent adjudication committee. In the event of doubt, a complete blind patient record will be prepared by the clinical research associates. Two independent experts blinded to the randomization arm will classify these episodes according to infection definitions (see below). In case of disagreement, the opinion of a third expert will be sought.

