### Definitions

French [9] and American [7] guidelines will be used by the blind adjudication committee.

– Catheter colonization will be defined as a quantitative culture tip showing at least one micro-organism at a concentration of 1,000 colonies forming 1 unit per milliliter (cfu/mL) or more.

– Catheter-related sepsis without bacteremia will be defined according to the combination of (1) fever (body temperature ≥38.5°C) or hypothermia body temperature ≤36.5°C), (2) catheter colonization, (3) regression of fever or hypothermia within the 48 h following catheter removal and without any change of antimicrobial therapy, or presence of pus at catheter insertion site, and (4) no other source of infection identified.

– Catheter-related bloodstream infection will be defined as the combination of (1) fever (body temperature ≥38.5°C) or hypothermia body temperature ≤36.5°C), (2) one or more positive peripheral blood cultures drawn 48 h before or after catheter withdrawal, (3) isolation of the same organism (same species and same susceptibility pattern) from the colonized catheter, or from the catheter insertion site, or a blood-culture differential time-to-positivity of 2 h or more, and (4) no apparent source of bacteremia other than the catheter. In patients with positive coagulase negative staphylococci bacteremia, at least two positive cultures obtained from separate blood samples will be mandatory.

– Major catheter-related infections will be either catheter-related sepsis without bacteremia or catheter-related bloodstream infections.

– Non-cultured catheters or catheters growing under 1,000 cfu/mL will be classified as catheter-related sepsis or bloodstream infections in case of sepsis without or with bacteremia and no other detectable source.

– Non-cultured catheters will be classified as not colonized unless there was sepsis with no other detectable cause.

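### The Kaplan-Meier risk curves treat event-free removal and death as censoring and so overstate the risk catheters actually run; for colonization, the hazard ratio also depends on equal removal timing between arms

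*Protocol article*

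**What the plan says.** The Statistical analysis section of the protocol article plans that "Kaplan-Meir curves of the risks of major-CRI and CR-BSI and catheter colonization will be plotted for each treatment group". For effects it says that "Analysis of antiseptic efficacy will be carried out using a marginal Cox model stratified by centers", with a robust variance for several catheters per patient, and adds that "This model takes into account the censored nature of the data". It then says that, absent interaction, the scrubbing and chlorhexidine effects are analyzed independently. It names no event date for colonization, no rule for catheters removed without the event or for deaths, and no competing-risk method.

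Colonization is a laboratory result on the removed tip. The abstract says "At catheter removal, catheter tips will be quantitatively cultured", the Cultures section says "Catheters will be removed aseptically and their distal 5cm will be sectioned with sterile scissors", and under Definitions "Catheter colonization will be defined as a quantitative culture tip showing at least one micro-organism at a concentration of 1,000 colonies" per milliliter, or more. Catheters without a culture are covered by a rule: "Non-cultured catheters will be classified as not colonized unless there was sepsis with no other detectable cause".

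On removal, the section on catheter insertion and maintenance says "The decision to remove the catheter will be made solely by the patient’s physician". Study design states that physicians and nurses are not blinded to the antiseptic. Under Outcomes, the second endpoint, on scrubbing, is judged on colonization. Assessment endpoints expresses infection and colonization as incidence densities.

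**The concern.** There are two separate issues.

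*Curves.* A catheter that has been taken out, or whose patient has died, can no longer become infected. Kaplan-Meier treats it as if it stayed at risk unobserved. Its complement then describes a setting in which no catheter is ever removed, which is not what readers understand by the risk of a catheter infection. This needs no difference between arms and affects all three plotted endpoints.

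*Colonization hazard ratio.* Because the tip is cultured once, onset is never seen and removal is the only date the data can supply. If that date is used as the event time, the modeled event is removal of a colonized catheter, and its hazard contains the removal hazard. If removal were faster in one arm, the ratio would move without any effect on colonization. This touches the scrubbing objective, which aims to show that scrubbing brings no reduction: a real benefit could be masked, or a false difference produced.

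**Working it through.** **The plan's own figures.** Sample size calculation equates 5% of catheters with 4 per 1,000 catheter-days, so mean dwell is 0.05/0.004 = 12.5 days. The stated size also reproduces: 5% against 2.5%, 80% power, two-sided 5%, pooled variance and no continuity correction give 906 catheters per arm, and 906/2 = 453 patients. Nothing below changes that number.

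**Infection curve.** Assume constant hazards: infection 0.004 per day, event-free removal or death 1/12.5 = 0.08 per day.

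- 1 minus Kaplan-Meier estimates 1 − exp(−0.004t).
- Cumulative incidence is 0.004/0.084 × (1 − exp(−0.084t)).

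| Day | 1 − KM | Cumulative incidence | Ratio |
|---|---|---|---|
| 14 | 5.4% | 3.3% | 1.7 |
| 28 | 10.6% | 4.3% | 2.5 |

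If 12.5 days is instead the mean dwell of all catheters, cumulative incidence is 0.05 × (1 − exp(−0.08t)), or 3.4% and 4.5%, and the conclusion is the same. The Kaplan-Meier complement passes 5% at −ln(0.95)/0.004 = 12.8 days and by day 28 is about twice the share of catheters the plan expects to be infected in total.

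**Colonization curve.** For illustration, take the povidone iodine arm of the randomized trial summarized under Background: 22.2% colonized, 18.3 per 1,000 catheter-days, so mean dwell 0.222/0.0183 = 12.1 days. Assume exponential dwell and removal as the event date.

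- Colonized at insertion: at day 28, 1 − KM = 1 − exp(−0.222 × 28/12.1) = 40.2%, and cumulative incidence = 0.222 × (1 − exp(−28/12.1)) = 20.0%.
- Colonized at a constant rate during dwell: 46.2% against 16.3%.

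The excess is thus 2 to 3 times at day 28. Against a different target, the chance that a catheter is already colonized by day t, the direction varies. The curve reads 12.1% against 22.2% at day 7 in the first case, 40.2% against 22.2% at day 28 in the first case, and 15.8% against 28.1% at day 14 in the second.

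**Colonization hazard ratio.** Let r(t) be the removal hazard and P(t) the share colonized among catheters removed at dwell t. The hazard of being removed colonized is r(t) × P(t), so

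HR(t) = [r1(t)/r0(t)] × [P1(t)/P0(t)].

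Simulated results, with colonization at insertion, 22.2% in the reference arm, 2,400 independent catheters per arm and 60 runs per setting:

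| True ratio of shares | Mean dwell in one arm | Cox HR | Runs rejecting |
|---|---|---|---|
| 1.00 | equal | 1.00 | 2% |
| 1.00 | 10% shorter | 1.12 | 50% |
| 1.00 | 20% shorter | 1.24 | 93% |
| 0.75 | equal | 0.74 | 100% |
| 0.75 | 20% shorter in the better arm | 0.93 | 10% |

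The null values agree with the identity (1/0.9 = 1.11, 1/0.8 = 1.25). A constant removal ratio leaves hazards proportional, so the planned check of Schoenfeld residuals would not reveal it.

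**The alternative model.** Take colonization at an assumed 0.012 per day in both arms, removal at 0.15 per day, and removal 10% or 20% faster in one arm. A complementary log-log regression on log dwell returns about 1.0 in both cases if removal is unrelated to colonization, where Cox gives about 1.1 and 1.2. If the removal hazard triples once a catheter is colonized, the same regression gives 0.95 and 0.90, and Cox 1.03 and 1.06.

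**The case against.** The strongest reply is that much of this is inferred. The article gives no event date for colonization and no rule for deaths, and it ties the Cox model expressly to antiseptic efficacy; its use for scrubbing and colonization is implied. Such details commonly sit in a full protocol or analysis plan that is not shown. That stands for the hazard ratio. It does not remove the point on the curves, because the method is named and Kaplan-Meier has no treatment of other removals except censoring.

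A reader might go further and infer that the planned colonization hazard ratio is biased. The documents do not support that. Patients are randomized, so equal removal timing is the default, and under it the Cox comparison is valid. No passage reports a difference; the 10% and 20% are illustrations. Lack of blinding is attributed to the color of the antiseptics, and the scrubbed and unscrubbed groups contain the same two agents.

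A reader might also infer that a complementary log-log model should replace Cox. It should not: it conditions on dwell time, which arises after randomization. It also needs removal to be independent of colonization, whereas the Cultures section anticipates catheters removed with systemic or local signs. When that independence fails, it can lie further from the truth than Cox.

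Finally, the curves are descriptive and the assessed measure is incidence density. That is correct and limits the consequence to what the figures convey.

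**Conclusion.** The point on the curves holds. Plotted as risks, they overstate cumulative incidence by about 1.7 times at day 14 and 2.5 times at day 28 for infection at the plan's own rate, and by about 2 to 3 times at day 28 for colonization at the illustrative 22.2%. The exact factors rest on exponential times. The direction does not, as long as catheters leave without the event. The statement concerns cumulative incidence only; it should not be read as saying that the colonization curve always exceeds the latent risk of being colonized, which it can also understate.

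The point on the hazard ratio is conditional. With colonization known only at removal, the ratio carries the removal-rate ratio as a factor. It is sound if timing is equal across the compared arms and distorted otherwise. Open-label removal decisions make a difference possible, and the planned diagnostics would not detect a constant one. This matters mainly for the scrubbing endpoint. Neither part undermines the marginal Cox model for major catheter-related infection or the sample size.

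**What to change.** 1. Replace the Kaplan-Meier plots for major infection, bloodstream infection and colonization by cumulative incidence curves, with event-free removal and death as competing events.
2. State that colonization is dated at removal, and how event-free removals and deaths enter the Cox model.
3. Keep the marginal Cox model, and report catheter dwell time by randomized arm beside the colonization result.
4. Add, as a sensitivity analysis only, a binary regression of colonization at removal, clustered by patient (for example complementary log-log with log dwell, center, antiseptic and scrubbing). State that it assumes removal is independent of colonization and is biased if that fails. An unadjusted proportion does not serve in its place when colonization accrues during dwell: with 0.012 per day in both arms and removal at 0.15 or 0.18 per day, the shares are 0.012/0.162 = 7.4% and 0.012/0.192 = 6.3%, although colonization rates are equal.

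The cost is wording and standard code. Insertion and removal dates and tip cultures are already listed under Data collection, and no sample size changes. The drawback is that plotted risks will look lower and compare less directly with earlier trials.
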